Electroconvulsive therapy (ECT) remains the gold standard in treating severe and/or treatment-resistant MDEs [15]. Response rates to ECT are high (50–80%), and latency to response is shorter than for classical pharmacotherapy [16–18]. Despite these benefits, access to ECT is limited and lengthy wait-lists are common. Moreover, its high costs, potential for side effects, including cognitive deficits, and enduring stigma have resulted in underutilization of ECT as a treatment for MDEs.

One of the current goals in psychiatry is the identification of biological phenotypes (or biomarkers) that could improve characterization of the likelihood that a patient will respond to a specific treatment strategy. This is particularly pertinent in context of ECT or ketamine treatment, as both are currently reserved for the most treatment resistant and severely depressed patients. Candidate biomarkers for outcome prediction in depression include structural and functional neuroimaging profiles, as well as genetic, epigenetic, proteomic, and metabolic features [19]. Currently, it is unclear how baseline biomarker measures moderate clinical outcomes. Exploring how these measures are impacted by ECT or ketamine may further our understanding of the underlying mechanisms of action of these interventions in alleviating depressive symptoms.

The primary objective of this longitudinal, multi-centre non-inferiority trial is to compare acute treatment of MDEs with repeated IV ketamine and ECT in terms of efficacy, speed of therapeutic effects, side effect profiles, and health care resource utilization. A secondary objective is to assess whether ketamine response can be sustained with a gradual spacing of ketamine maintenance infusions, as is the case for ECT. Finally, through the collection of clinical, cognitive, neuroimaging and molecular data according to Canadian Biomarker Integration Network in Depression (CAN-BIND) protocols [20, 21], we aim to identify biomarkers that predict or moderate ketamine or ECT response.

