### Data analyses

The primary outcome measure is the rate of antidepressant response (i.e., percentage of participants meeting antidepressant response criteria [≥ 50% reduction in MADRS scores from baseline and MADRS score < 22]) in each arm at the end of the randomized treatment phase. A total of 240 participants will be enrolled into the randomized treatment phase across the four recruiting sites. This will allow for a 20% drop-out rate (i.e., withdrawal of approximately 40 participants), resulting in a total sample of *N* = 200. For the primary efficacy analyses, a non-inferiority margin of 20% was selected based on clinical judgment. Thus, a sample of 200 participants (*N* = 100/treatment arm) is required to be 90% certain that the upper limit of a one-sided 95% confidence interval will exclude a difference in favour of the ECT group of more than 20%. Secondary efficacy outcomes will include percent change in MADRS scores from baseline to the end of the randomized treatment phase, and remission rates (MADRS score ≤ 10). Response and remission rates will also be assessed for the crossover phase. Clinical scores will be analyzed using linear mixed models (appropriate covariates, such as site, will be included, as needed). Categorical outcomes (response/remission) will be examined using χ^2^ tests. The alpha will be set at 0.05.

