Speed of therapeutic effects is defined as the number of treatments required for participants to first meet antidepressant response criteria. A Kaplan-Meier survival analysis will be used to compare the mean number of required treatments for first response to ECT and ketamine during the randomized treatment phase. Side effect burden will be quantified by summing the total frequency and severity scores of the TSES administered after the final treatment during the randomized treatment phase. Mean total TSES scores for ECT and ketamine will be compared using an ANOVA (appropriate covariates will be included). Further, side effect profiles for each treatment will be derived by identifying the most common side effects reported in each arm of the trial (present in > 5% of participants). Treatment tolerability will be estimated via dropout rates. Finally, data from CNS Vital Signs will permit comparison of any cognitive side effects associated with ECT or ketamine (compared at the end of the randomized treatment phase). Level of health care utilization (estimated using average cost of treatment administration, number of days of inpatient hospitalization, and frequency of outpatient consultations) associated with ECT and ketamine will be compared using ANOVAs.

The main outcome in the maintenance phase will be time to relapse. Due to differences in the administration schedules of ECT and ketamine during maintenance, two parallel descriptive statistics will be outlined. For each treatment, mean time to relapse (loss of antidepressant response) will be estimated using Kaplan-Meier survival analysis.

While data from each analytical platform will be analyzed independently using the methods described herein and elsewhere [21], integration of data collected across platforms will also be carried out, and will be overseen by the CAN-BIND Data Science Advisory Team comprised of Principal Investigators, domain-specific informatics advisors, and operations support. In addition to conventional statistical approaches, machine-learning approaches will be applied particularly with regards to outcome prediction (i.e., response/non-response to ECT and ketamine at 3 or 4 weeks of treatment).

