This trial is comparing the efficacy, speed of therapeutic effects, side effect profiles, and health care resource use associated with ketamine and ECT. As a non-inferiority trial, we expect ketamine to exhibit similar efficacy rates as ECT yet with more rapid antidepressant effects, less side effects, and with substantially less cost and health care resource use. This study is among the first to directly compare these treatments using a randomized design, complementing an ongoing, large-scale, parallel-arm clinical trial comparing ketamine and ECT for treatment-resistant depression in the United States (the ELEKT-D trial) [53]. Unique aspects of our trial include the crossover design, where participants who do not respond to the first randomized treatment may crossover to receive treatment with the alternate strategy, longer-term treatment and follow-up through the maintenance phase, and the inclusion of individuals with either unipolar or bipolar depression. Ketamine and ECT are both effective treatments for BP [54, 55], although, the assessment of effective and long-lasting treatments in the context of BP has received substantially less attention than that of unipolar depression.

Another strength of the current study is that both treatment arms are administered under comparable conditions. There is a balanced frequency of treatment administration in each arm during the acute treatment phases. Moreover, ECT and ketamine treatments are administered in the same setting at each site, reducing variability that could arise due to numerous confounding factors. Finally, since treatments cannot be blinded from participants or from clinical and research staff, clinical ratings are being conducted by raters who are blind to the treatment and are otherwise not involved in the trial. This rigorous study design allows for the relatively unbiased evaluation of the antidepressant effects of ketamine relative to an active comparator, addressing a critical gap in this area.

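### Separate > 5% lists for each arm cannot by themselves support the planned comparison of side effect profiles for effects near the cut

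*Protocol article*

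**What the plan says.** The Background section words the primary objective as follows: "compare acute treatment of MDEs with repeated IV ketamine and ECT in terms of efficacy, speed of therapeutic effects, side effect profiles". Resource use is the fourth item in that list. The Discussion repeats that profiles are among the things compared: "This trial is comparing the efficacy, speed of therapeutic effects, side effect profiles, and health care resource use associated with ketamine and ECT". It also states the expectation that ketamine will show "similar efficacy rates as ECT yet with more rapid antidepressant effects, less side effects".

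The Data analyses section plans several safety summaries:

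- The total TSES score (frequency and severity summed, after the last randomized-phase treatment) is compared between arms by ANOVA.
- Dropout rates serve as the measure of tolerability.
- CNS Vital Signs results are compared for cognitive effects.
- In addition, "side effect profiles for each treatment will be derived". The method given for this is to list the effects that pass a frequency threshold: "identifying the most common side effects reported in each arm of the trial (present in > 5% of participants".

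The last item is the only statement of how profiles are produced. The article mentions no list common to both arms and no comparison of individual side effects between arms. The same section gives the planned evaluable number as "100/treatment arm) is required to be 90% certain" for the primary analysis, from 240 enrolled.

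**The concern.** A profile is meant to show which side effects distinguish two treatments. Under this rule each arm's profile depends only on which effects cross 5% in that arm. With about 100 patients, one patient can decide whether an effect is listed. An effect seen in 6 ECT patients and 5 ketamine patients enters the ECT profile and not the ketamine profile, although Fisher's exact test gives p = 1.0.

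The rule can also mislead in the other direction. Two effects that both exceed 5% are listed alike, however far apart their rates are.

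Readers tend to take presence on one list and absence from the other as a safety difference. Here the treatments cannot be blinded from participants or clinical staff, and the authors expect fewer side effects with ketamine. The item-level comparison should therefore rest on something firmer than list membership.

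**Working it through.** **Inputs from the protocol article (Data analyses; 1:1 allocation from Protocol overview)**

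- Listing rule: observed rate above 5%, by arm.
- Evaluable patients: 100 per arm. Enrolled: 240, so 120 per arm.
- The article describes the allowance as "This will allow for a 20% drop-out rate (i.e., withdrawal of approximately 40 participants". Since 20% of 240 is 48, the literal figure is (240 − 48)/2 = 96 per arm. All three sizes are checked below.

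**Inputs assumed.** The true rates of individual side effects, their number and their independence are not given, so ranges are shown.

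**Reproducing the planned 100 per arm.** The design response rate is not stated. Taking 65%, the midpoint of the 50–80% quoted for ECT in the Background, with a 20-point margin, one-sided alpha 0.05 and 90% power:

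n = (1.645 + 1.282)² × 2 × 0.65 × 0.35 / 0.20² ≈ 98 per arm.

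This agrees with about 100.

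**Chance of being listed.** At n = 100, above 5% means 6 or more patients. For true rate p, q = P(X ≥ 6), with X binomial (100, p). If both arms share the same p, the chance that exactly one arm lists the effect is 2q(1 − q), which cannot exceed 0.50.

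| True rate, both arms | q | Listed in one arm only |
|---|---|---|
| 2% | 0.015 | 0.03 |
| 3% | 0.081 | 0.15 |
| 4% | 0.212 | 0.33 |
| 5% | 0.384 | 0.47 |
| 6% | 0.559 | 0.49 |
| 7% | 0.709 | 0.41 |
| 8% | 0.820 | 0.30 |
| 10% | 0.942 | 0.11 |
| 15% | 0.998 | 0.003 |

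Example at 5%: 2 × 0.384 × 0.616 = 0.47. At 96 per arm (5 or more patients needed) the figure is 0.50, and at 120 per arm (7 or more needed) it is 0.48. The choice of n does not matter much.

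**Unequal rates that look alike.** With true rates of 8% and 30%, the listing chances are 0.820 and essentially 1. Both lists carry the effect with probability about 0.82.

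**Unequal rates on either side of the cut.** With true rates of 15% and 2%, only the higher-rate arm lists the effect with probability 0.998 × (1 − 0.015) = 0.98. Far from the cut, the lists do inform.

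**Whole lists.** With equal true rates and independent effects, the chance that the two lists differ somewhere is 1 − Π[1 − 2q(1 − q)]. At 100 per arm:

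| Assumed true rates, same in both arms | Chance the lists differ |
|---|---|
| Ten at 20–30%, ten at 1% | 0.01 |
| Ten at 15%, ten at 2% | 0.29 |
| One at 5%, the rest far from the cut | 0.48 |
| Two at 5% | 0.72 |
| Twenty at 2, 4, …, 40% | 0.80 |
| Twenty at 1, 2, …, 20% | 0.96 |

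**Under one common list.** An effect above 5% in either arm is shown for both, so the lists cannot disagree. An effect with a true rate of 5% in both arms is listed with probability 1 − 0.616² = 0.62 (0.16 at 3%, 0.92 at 7%).

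The difference then carries the message, here with simple normal-approximation intervals:

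- 6/100 against 5/100: 1 point, standard error √(0.06 × 0.94/100 + 0.05 × 0.95/100) = 0.032, 95% interval about −5.3 to 7.3 points.
- 8/100 against 30/100: 22 points, standard error √(0.08 × 0.92/100 + 0.30 × 0.70/100) = 0.053, 95% interval about 11.6 to 32.4 points.

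**The case against.** The strongest reply is that the formal between-arm comparison lies elsewhere. The total TSES score is tested without any frequency cut, and it bears most directly on the expectation of fewer side effects. The profile is an added descriptive list of common effects, with no test or conclusion attached to membership. Nothing in the sentence forbids showing both arms' counts beside each listed effect, and a frequency threshold is a common reporting choice.

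Much of this stands, and it limits the point to the item-level comparison. It does not remove it. A summed score cannot show which side effects differ, the article says profiles are compared, and the only rule it gives for them works arm by arm.

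Three stronger readings are tempting, and the documents do not support them:

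- A reader might infer that the two profiles will usually differ even when the treatments have identical rates. That depends on how many effects lie close to 5%. The article does not say, and the scenarios run from 0.01 to 0.96.
- A reader might infer that a difference between lists carries almost no information. That is so only near the cut. At 15% against 2% the lists point the right way 98% of the time.
- A reader might infer that any harm at or below 5% is lost. An effect observed at 5% or less leaves only that arm's list. TSES-rated effects still count in the total score, and the Treatments section provides an adverse event log and a safety monitoring board.

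The absence of tables for serious events and for discontinuations is not a fault here, because a condensed article may leave them to the full protocol or the analysis plan.

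**Conclusion.** The point holds in limited form. A stated rule serves a stated aim poorly: with about 100 per arm, an effect with an equal true rate of 4% to 7% is listed for one arm only in 33% to 49% of trials, and clearly different rates above the cut usually look the same. Membership of a list alone therefore cannot support an item-level comparison for effects near 5%.

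The per-effect figures rest on the arm-by-arm reading of the sentence, on binomial counts and on independent arms, and they change little between 96 and 120 per arm. No single figure can be given for how often the complete lists differ. The primary efficacy analysis and the TSES total score analysis are unaffected.

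**What to change.** In Data analyses, replace the per-arm listing with wording such as: *Any side effect present in more than 5% of participants in either arm during the randomized treatment phase will be tabulated for both arms, with counts, rates and a 95% confidence interval for the difference. Profiles will be compared through these differences, not by which effects cross 5%.*

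The cost is one or two sentences and a slightly longer descriptive table, using data already collected on the TSES and in the adverse event log. The intervals would be unadjusted for the number of effects examined, and the table should say so.

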### Procedure

Individuals first provide signed consent to receive ECT as part of their care. Subsequently, at the screening visit, all participants provide written informed consent in adherence with Good Clinical Practice guidelines before initiation of any study related procedures. Participants then undergo a full medical work-up to ensure ECT and ketamine treatment suitability, which includes a medical history, physical examination*,* height, weight and vital signs measurements, 12-lead electrocardiogram, urinalysis, standard clinical laboratory tests, toxicology and pregnancy screenings, as well as recording of concomitant medication regimens. Participants are also assessed for contraindications to magnetic resonance imaging (MRI). They then undergo a psychiatric interview to confirm a diagnosis of MDD or BP according to Diagnostic and Statistical Manual for Mental Disorders, fifth edition (DSM-5) [23] criteria using the MINI International Neuropsychiatric Interview (MINI) Version 7.0.2 [24]. Depressive symptom severity is assessed using the MADRS, while lifetime history of suicidal ideation, behaviours, and attempts are assessed using the Columbia-Suicide Severity Rating Scale (C-SSRS) [26]. Absence of cognitive impairment is ascertained with the Montreal Cognitive Assessment (MOCA) [25]. An up-to-date Antidepressant Treatment History Form (ATHF) [27] is used to assess pharmacological treatment history (type, dose, duration). Participants provide sociodemographic information using standardized self-report forms and complete various self-report questionnaires assessing their pre-treatment psychiatric symptoms and quality of life.

Following the screening visit, eligible participants are formally enrolled in the study, randomized, and undergo baseline data collection, including a computerized cognitive battery, an MRI scan, and blood draws for genomic and molecular markers.

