At each treatment visit, clinical providers assess treatment response, side effects, adverse events and suitability for continued treatment. All reasonable efforts will be made to retain participants in the study without exerting undue pressure. Interventions may be discontinued based on clinical judgement in accordance with the risk-benefit ratio. Side effects are recorded using the clinician-rated Toronto Side Effect Scale (TSES) [30] and an adverse event log. A Data and Safety Monitoring Board (DSMB) has been assembled to monitor participant safety and treatment efficacy during the trial. This panel is comprised of three study independent experts: a psychiatrist, an anesthesiologist, and a statistician. Healthcare resource use occurring outside of the study, such as inpatient hospitalization, emergency room visits or outpatient consultations, is also documented at each visit. Finally, the estimated financial cost of administering each treatment is being calculated at each site.

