#### Cognitive assessment

A computerized neurocognitive test battery is administered prior to treatment initiation and at the completion of each treatment phase (Fig. 1). CNS Vital Signs [40] is a battery comprised of well-established cognitive tests including verbal and visual memory, finger tapping, symbol digit coding, Stroop Test, a test of shifting attention, and continuous performance test. Cognitive testing is being used to assess and compare potential effects of repeated ECT and ketamine treatment on cognitive function, and as a possible marker of response prediction.

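### The cognitive comparison names no baseline term, and the side-effect burden score rests on one rating taken after unequal numbers of treatments

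*Protocol article*

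**What the plan says.** **Cognition.** Under Cognitive assessment: "A computerized neurocognitive test battery is administered prior to treatment initiation and at the completion of each treatment phase". The purpose is given there too: "Cognitive testing is being used to assess and compare potential effects of repeated ECT and ketamine treatment on cognitive function". Data analyses then says that these data "will permit comparison of any cognitive side effects associated with ECT or ketamine (compared at the end of the randomized treatment phase"). It names no model, covariate or change from baseline for this outcome. On the order of events, the Procedure section says that "eligible participants are formally enrolled in the study, randomized, and undergo baseline data collection, including a computerized cognitive battery".

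**Side effects.** Under Treatments: "At each treatment visit, clinical providers assess treatment response, side effects, adverse events and suitability for continued treatment". The instruments named there are the TSES and an adverse event log. Data analyses defines burden by "summing the total frequency and severity scores of the TSES administered after the final treatment during the randomized treatment phase", and adds: "Mean total TSES scores for ECT and ketamine will be compared using an ANOVA (appropriate covariates will be included"). It also plans a profile of side effects present in more than 5% of participants, and uses dropout rates for tolerability.

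**Course length.** Under Randomized treatment phase, the treating physician chooses 9 or 12 ECT sessions. On ketamine, patients in remission after 9 infusions leave the phase, while responders not in remission go on to 12. In both arms, non-responders after 3 weeks may cross over.

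**The concern.** Side-effect profile is part of the stated primary objective (Background), and the Discussion expects fewer side effects with ketamine. These comparisons therefore carry weight, even though they are not the primary efficacy endpoint.

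For cognition, patients aged 18 to 70 will differ widely before any treatment. An analysis of end scores alone leaves those differences in the error term, although the baseline score that would remove part of them is already collected.

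For side effects, one rating at the close of the course describes the patient's state at that moment. A side effect that was troublesome in week 1 and gone by week 3 adds nothing to the score. The moment itself is not common to all patients: it depends on a physician's choice in one arm and on MADRS results in the other. Randomization does not balance this, because it arises after allocation.

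**Working it through.** The plan gives no sample-size or power figure for either comparison. Its 100 per arm comes from the primary non-inferiority calculation (20-point margin, one-sided 5%, 90% power). With a common response rate of 0.63, which the article does not state, that calculation is (1.645 + 1.282)² × 2 × 0.63 × 0.37 / 0.20² ≈ 100. The figure has no bearing on this point; it is borrowed below only as a number of patients.

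**Cognition**

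Inputs: n = 100 per arm (Data analyses); two-sided 5% (alpha of 0.05 is stated, two-sided is assumed); baseline-to-end correlation r (assumed, since the article gives none).

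1. End scores only: detectable difference at 80% power = (1.960 + 0.842) × √(2/100) = 0.396 SD.
2. Adjustment for baseline multiplies the variance by 1 − r², so the detectable difference becomes 0.396 × √(1 − r²).
3. Power at a true difference of 0.4 SD (an illustrative size) = Φ(0.4 / (√(1 − r²) × √(2/100)) − 1.960).
4. Equivalent unadjusted sample per arm = 100 / (1 − r²).

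| r (assumed) | Variance cut | Detectable difference (SD) | Power at 0.4 SD | Equivalent n per arm |
|---|---|---|---|---|
| no adjustment | 0% | 0.396 | 80.7% | 100 |
| 0.3 | 9% | 0.378 | 84.3% | 110 |
| 0.5 | 25% | 0.343 | 90.4% | 133 |
| 0.7 | 51% left, 49% cut | 0.283 | 97.7% | 196 |
| 0.8 | 64% | 0.238 | 99.7% | 278 |

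A plain change score is not an equal substitute. Its variance factor is 2(1 − r), which exceeds 1 when r is below 0.5. At r = 0.3 the factor is 1.4 and power at 0.4 SD drops to 66.7%.

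The order of events limits the adjusted analysis. The Procedure section lists randomization before the baseline battery, and the Discussion says participants cannot be blinded. If knowing the allocation shifted baseline scores by δ between arms and did not carry over to the end scores, the adjusted estimate would move by −β × δ, where β is the regression slope on baseline. The unadjusted end-of-phase comparison does not use the baseline and is free of this.

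**Side effects**

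1. The final treatment is number 9 or 12, or earlier in a patient who stops. The rule is clinical choice for ECT and MADRS response for ketamine.
2. Nine treatments is the shortest planned course in both arms, so the first nine form a window of equal planned exposure.
3. For k ratings with equal within-patient correlation ρ (assumed), the variance of their mean relative to one rating is (1 + (k − 1)ρ)/k. For k = 9 this is (1 + 8 × 0.3)/9 = 0.38 at ρ = 0.3, 0.56 at ρ = 0.5 and 0.73 at ρ = 0.7.
4. These ratios are only a guide. A per-visit analysis estimates burden over the course, which is a different quantity from burden at its end. They also assume a TSES score at each of the nine visits.

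**The case against.** **The article does not exclude a baseline covariate.** It gives a time point, and a baseline-adjusted comparison is also made at the end of the phase. Table 2 lists CNS Vital Signs among the clinical assessments, and Data analyses promises linear mixed models with covariates for clinical scores. A condensed article may leave the covariate list to a fuller document. This stands. A reader might infer that the baseline battery goes unused or that the end-score comparison is biased, and the text supports neither. What remains is that change from baseline is named for MADRS and covariates for the TSES, while cognition has neither.

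**Earlier side effects are not lost to the trial.** The profile of side effects above 5%, the adverse event log and the dropout rates are not tied to the final visit. This stands in part: they record that a side effect occurred, but none of them compares the amount of burden between arms.

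**End-of-course burden is a legitimate quantity,** above all for effects that accumulate, and a nine-treatment window leaves out ratings 10 to 12. This stands, and is the reason to add an analysis and keep the final score.

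**The number of TSES ratings is not certain.** Treatments says that side effects are assessed at every treatment visit and recorded on the TSES. A full score each time is the natural reading but is not stated word for word.

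**Disclosure before the battery is not stated.** The Procedure section gives an order of events, not the moment at which patients learn their arm. A reader might infer that baseline cognition is contaminated; the text shows only that this is not ruled out.

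**Conclusion.** The point holds as an inexpensive improvement to two secondary comparisons. It does not touch the primary efficacy analysis.

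The side-effect part is the firmer one, because the definition is explicit. The burden score depends on one rating at a time set by arm-specific and response-dependent rules. It omits side effects that resolved, and early stoppers are either missing or rated at lower exposure. The size of the effect on the comparison cannot be derived from the article.

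The cognitive part is a loss of precision, not of validity, provided the data are complete. It arises only if the analysis follows the article's wording without a baseline term. The gain from adjustment is a variance cut of 9% to 64% for r of 0.3 to 0.8; both r and ρ are assumptions.

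**What to change.** 1. **Cognition.** State that each CNS Vital Signs domain is analysed by ANCOVA or a mixed model with baseline score, centre and age as covariates. Keep the unadjusted end-of-phase comparison as a sensitivity analysis, because the baseline battery is listed after randomization.
2. **Side effects.** Add a repeated-measures analysis of TSES scores, with centre in the model, over the first 9 treatments. Use all available ratings, including those of patients who stop early. Report it beside the final-treatment score, which remains a valid end-of-course measure.
3. **Order of events.** For patients still to be enrolled, complete the baseline cognitive battery before the allocation is disclosed.

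Items 1 and 2 need only analysis wording and use data that the trial already collects. If the TSES is not scored at every visit, item 2 runs on the ratings that exist. Item 3 reorders one visit; its small downside is a few batteries completed by patients who are then not randomized.

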### Treatment schedule

#### Randomized treatment phase

For participants receiving ECT, the number of treatments (9 or 12) is determined by the treating physician. For the ketamine arm, the number of treatments is determined by participants’ antidepressant response as assessed using the MADRS. Participants achieving remission (MADRS ≤10) after 9 ketamine infusions exit the randomized treatment phase and are eligible to enter the maintenance phase (Fig. 1). Participants receiving ketamine who achieve an antidepressant response but not remission after 9 treatments receive an additional 3 infusions (12 treatments total). In both treatment arms, non-responders (< 50% MADRS decrease or a score ≥ 22) after 3 weeks may crossover to receive a full course of treatment with the alternative strategy. Responders after 12 treatments may move on to the maintenance phase.

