#### Crossover phase

Participants only enter the crossover phase if they do not meet antidepressant response criteria at the end of the randomized treatment phase. During the crossover phase, ECT non-responders receive a course of 9 or 12 ketamine infusions, while ketamine non-responders undergo 9 or 12 ECT sessions. Non-responders at the end of the crossover phase exit the study. Those meeting the response criteria after the crossover phase (≥ 50% MADRS score decrease relative to pre-crossover score and MADRS score < 22) may enter the maintenance phase.

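### The health care utilization outcome leaves out the emergency room visits that the trial records at each visit, and it should name its comparison window

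*Protocol article*

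**What the plan says.** In the protocol article, the Treatments section says that health care use outside the study, "such as inpatient hospitalization, emergency room visits or outpatient consultations, is also documented at each visit". That names three kinds of outside care. The same section says that the cost of giving each treatment is worked out at each site.

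The Data analyses section then builds the outcome. Utilization is "estimated using average cost of treatment administration, number of days of inpatient hospitalization, and frequency of outpatient consultations", and the levels "associated with ECT and ketamine will be compared using ANOVAs". Two of the three kinds of outside care are carried forward. Emergency room visits are not, and no reason is given.

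The utilization sentence names no period. The sentence just before it, on cognition, does: "compared at the end of the randomized treatment phase". The Background gives the main pointer to the intended period. Its primary objective reads, in part: "compare acute treatment of MDEs with repeated IV ketamine and ECT in terms of efficacy, speed of therapeutic effects, side effect profiles, and health care". The last item in that list, cut short here, is use of resources, so the outcome sits under acute treatment. The Abstract frames it the same way.

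**The concern.** The article expects ketamine to cost substantially less and to need substantially less care (Discussion), and it describes ketamine as a potentially less expensive alternative (Conclusion). The utilization comparison is what would support or undercut those statements.

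The Treatments section lists emergency visits separately from hospital stays and from outpatient consultations. A visit that ends without admission therefore adds nothing to any of the three components in Data analyses. If such visits differ between the arms, in either direction, the planned comparison will not show it, even though the data are in hand.

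The missing period is a smaller matter. Participants can pass through a randomized phase, a crossover phase and six months of maintenance, and those who cross over receive both treatments. The sentence should say which part of this the comparison covers.

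**Working it through.** The article states no figure for this outcome, so there is none to reproduce. The check compares the passages and then works out observation time.

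**1. Components, recorded against analysed**

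| Item | Treatments section (recorded) | Data analyses section (analysed) |
|---|---|---|
| Inpatient hospitalization | yes | yes, as days |
| Emergency room visits | yes | no |
| Outpatient consultations | yes | yes, as frequency |
| Cost of giving treatment | yes, per site | yes, as an average |

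One recorded item is dropped.

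**2. Length of the randomized phase** (Randomized treatment phase section)

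- ECT: "the number of treatments (9 or 12) is determined by the treating physician", so 3 or 4 weeks at three per week.
- Ketamine: "the number of treatments is determined by participants’ antidepressant response as assessed using the MADRS". Remitters leave after 9 infusions (3 weeks). Responders short of remission go to 12 (4 weeks).
- Non-responders in both arms may cross over after 3 weeks.

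Per participant the largest difference is 28/21 = 1.33.

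For the arm means, let r be the ketamine response proportion, m the remission proportion, and q the share of ECT participants who have 12 sessions. Assume that ketamine non-responders leave at 3 weeks.

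- Ketamine mean = 3 + (r − m) weeks. ECT mean = 3 + q weeks.
- The article gives none of these values. Assumed pairs r/m are 50/25%, 60/30% and 70/40%, with q from 0 to 100%.
- Ketamine means: 3.25, 3.30 and 3.30 weeks.
- Lowest ECT:ketamine ratio: 3/3.30 = 0.91. Highest: 4/3.25 = 1.23.

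In the ketamine arm, length does not rise steadily with success: remitters and non-responders both leave at 3 weeks, and only those between them stay for 4.

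**3. Whole stay, for contrast only**

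The text does not state this reading. The Crossover phase section says "Non-responders at the end of the crossover phase exit the study", which puts exit at 3 + 3 to 4 + 4 = 6 to 8 weeks. A first-phase responder who completes 26 weeks of maintenance stays 3 + 26 = 29 to 4 + 26 = 30 weeks. Between these two extreme paths the ratio is 29/8 = 3.6 to 30/6 = 5.0.

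For the arm means, take an acute course of 3.5 weeks, first-phase response r1, crossover response r2, and no early exit:

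mean stay = 3.5 + 26·r1 + (1 − r1)(3.5 + 26·r2)

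- r2 = 40%, r1 = 50% against 60%: 23.45 and 24.66 weeks, ratio 1.05, difference 1.2 weeks.
- r2 = 30%, r1 = 40% against 60%: 20.68 and 23.62 weeks, ratio 1.14, difference 2.9 weeks.
- Equal r1 and equal r2 in both arms: ratio 1.0.

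**The case against.** **On emergency visits.** The list in the Treatments section is illustrative, and the definition in Data analyses is one parenthesis in a condensed article. Collecting an item does not oblige the plan to analyse it in this summary, and no visit rate is given to show that the result would change. This keeps the severity low. It does not remove the mismatch: the article itself spells out the components, names emergency visits as recorded, and then leaves them out without a reason.

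**On the window.** Resource use is tied to acute treatment in the Background and the Abstract. The utilization sentence closes the paragraph on acute outcomes, and maintenance starts in the next one. Side effect profiles and dropout rates in the same paragraph also carry no period. The window and the costing unit are details that an article usually leaves to the full protocol or SAP. This largely stands: the silence is not an error, and one clause would settle it.

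**On rates per week.** A 12-treatment course does use more resources than a 9-treatment course. Dividing by weeks observed can hide that, so total use per course is a legitimate target. This stands, and a weekly rate belongs beside the total, not in its place.

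**A stronger reading to resist.** A reader might infer that days and consultations are counted over the whole stay in the study, and that raw totals therefore penalise the arm with more responders four- to five-fold. The documents do not support this. Data analyses does not say that the whole stay is counted, and the objective points to the acute phase. The large ratio compares two extreme participants, not two arms.

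**Conclusion.** The omission holds on the plain text: emergency room visits are recorded at each visit but are not part of the utilization outcome, which belongs to the primary objective. Its effect on the comparison cannot be sized, because the documents give no visit rates.

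The window needs a clarifying statement, not a correction. If it is the randomized phase, as the objective suggests, observation differs by at most one week per participant. The ratio of arm means is 0.91 to 1.23 under the assumed response, remission and course-length shares. Those shares are assumptions; the article gives none of them.

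Severity is low. The data are already collected, and the primary analysis of response is unaffected. A full protocol or SAP that is not shown may define the window, but that would not by itself restore the missing component.

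**What to change.** In the Data analyses section:

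1. Add the number of emergency room visits to the components of health care utilization.
2. State that the main comparison is by randomized arm over the randomized treatment phase, in line with the acute-treatment objective in the Background.
3. Report use during crossover and maintenance separately and descriptively.
4. Keep total use per course as the main measure. Because the phase lasts 3 or 4 weeks under rules that differ by arm, add use per week observed as a sensitivity analysis.

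The cost is a few lines of analysis text and one extra summary. No new data are needed. The main comparison would cover a short period, with later use described only.
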